### Outcome measurement

#### Primary outcome

The primary outcome of this study will be change in the VAS score between baseline (visit 1) and completion of the intervention (visit 12) [30]. Using the 10-cm VAS (0, absence of pain; 10, the worst pain imaginable), the participants will be asked to report their degree of LBP.

#### Secondary outcomes

#### The secondary outcomes are:

Pain: change in the VAS score between baseline (visit 1) and week 2 (visit 4), week 4 (visit 8), week 6 (visit 12), and 4 weeks after completion of the intervention (visit 13). Additional clinical relevance will be compared as follows;
Based on previous studies [31, 32], the proportion of the minimal clinically important difference (MCID) in CLBP is defined as a 2 cm decrease on the VAS. The proportion of MCID (more than 2 cm decrease on the VAS) between baseline and visit 4, 8, 12, and 13 will be recorded.The proportion of participants who experience more than 30% decrease on the VAS between baseline and visit 4, 8, 12, and 13.The proportion of participants who experience more than 50% decrease on the VAS between the baseline and visit 4, 8, 12, and 13.Disability: to evaluate the physical disability due to low back pain, the Roland and Morris Disability Questionnaire (RMDQ) will be applied [33]. The RMDQ score is calculated by 24 items (in the range 0 (no disability) to 24 (maximum disability)). Change in score in the Korean version of the RMDQ will be compared between baseline and visit 4, 8, 12, and 13.Quality of life: to evaluate quality of life, the EuroQol-5D (EQ-5D) questionnaire will be applied. The EQ-5D measures five dimensions (mobility, self-care, activities of daily life, pain, and anxiety/depression) using a 1–3 scale, and a VAS to rate the current health state using a 0–100 scale [34]; change in the EQ-5D scores between baseline and visit 4, 8, 12, and 13 will be compared.Global assessment: to evaluate participants’ impressions of change, the Patient Global Impression of Change (PGIC) will be applied at visit 12 and 13. The PGIC is measured on 7-point scale (from 1 (completely recovered) to 7 (vastly worsened)) with a score of 1–2 indicating improvement, 3–5 no change, and 6–7 deterioration [35].Economic analysis: to evaluate the intervention-related cost, CEA and cost-utility analysis (CUA) will be conducted. Cost data will be collected separately as follows;
Medical cost: official medical costs will include benefit coverage by National health insurance and out-of-pocket payments such as for drugs and therapeutic equipment when visiting clinics or hospitals, for treating CLBP. Unofficial medical costs will include payments for over-the-counter drugs, dietary supplements, medical devices, orthotic devices, etc. which may be used without prescriptions by physicians.Non-medical cost: transportation costs, care costs, time costs, and lost productivity costs.Credibility test: to evaluate the credibility of Palmijihwang-hwan, a credibility/expectancy questionnaire will be applied at visit 1. Using a 9-point scale, a higher score indicates higher credibility and expectancy of Palmijihwang-hwan [36]

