#### Concomitant treatment

Other interventions including muscle relaxants, non-steroidal anti-inflammatory drugs (NSAIDs) (oral medication, topical application, or patch), antidepressant agents, anticonvulsants, treatments with Korean medicine (acupuncture, herbal medicine, and cupping), physical therapy, injections, or surgery will not be permitted during the treatment period (but are permitted during the follow-up period). However, concomitant medications taken within 4 weeks before trial participation or that are considered to have no effect on the interpretation of the results of this study may be allowed dependent on the judgment of the investigator.

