For CEA, combination treatment with Palmijihwang-hwan with acupuncture will be compared with acupuncture alone from a healthcare system perspective. The treatment cycle will be assumed to be 10 weeks. The treatment period (i.e. analysis period) can be the average life span if we build a model for the data analysis. If not, it is impossible to extrapolate the observations to the patient’s life span. Therefore, this part is omitted as of now. For health-related outcomes, the RMDQ will be used for CEA and the EQ-5D for CUA. The absolute cost-effectiveness ratio will be estimated for the combination treatment of Palmijihwang-hwan with acupuncture and for acupuncture monotherapy. The cost-effectiveness of the combination therapy will be evaluated based on the incremental cost-effectiveness ratio. All economic analysis will be performed using TreeAgePro R 1.1 (Williamstown, MA, USA, 2018).

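### Back-pain care barred in weeks 0–6 is also an item to be costed, and using it can end participation, so data behind the ICER are at risk

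*Protocol article*

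**What the plan says.** Four parts of the Protocol article bear on this point.

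- **What is costed** (Secondary outcomes, economic analysis). The stated aim is "to evaluate the intervention-related cost, CEA and cost-utility analysis (CUA) will be conducted". Official medical costs include "out-of-pocket payments such as for drugs and therapeutic equipment when visiting clinics or hospitals, for treating CLBP". The unofficial ones are described as follows: "Unofficial medical costs will include payments for over-the-counter drugs, dietary supplements, medical devices, orthotic devices, etc". Non-medical items are "transportation costs, care costs, time costs, and lost productivity costs".
- **Over what period** (Statistical analysis, economic paragraph). "The treatment cycle will be assumed to be 10 weeks". The combination is compared with acupuncture alone through an ICER, with RMDQ as the effect measure for cost-effectiveness and EQ-5D for cost-utility.
- **What care is barred** (Concomitant treatment). Muscle relaxants, NSAIDs in any form, antidepressants, anticonvulsants and other Korean medicine treatments are listed, and "physical therapy, injections, or surgery will not be permitted during the treatment period". The same care is allowed in the follow-up period. Some medications "may be allowed dependent on the judgment of the investigator".
- **What follows from using it** (Withdrawal criteria). One criterion is use, without the practitioner's permission, of treatment that affects the trial results. Another is any violation of the protocol. Both stand in one list with loss to follow-up and withdrawal of consent, and the list does not distinguish stopping study treatment from leaving the trial.

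**The concern.** For the items that appear both among the costs and in the ban, one event does two things: it generates a cost that the ICER should contain, and it can end the participant's time in the trial. Someone who obtains physiotherapy or an injection in week 3 without permission may leave then. That puts at risk not only the triggering cost but also every later cost, RMDQ and EQ-5D value up to visit 13.

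Reduced use of other care is one way in which an add-on treatment can offset its own cost, so losing users of other care matters to an incremental analysis. Unequal use is plausible here. Treatment is open-label, only one arm receives the herbal medicine, participants enter with VAS above 4 cm, and the Discussion says there is no rescue therapy and that this may affect compliance. Cost-effectiveness is one of the trial's stated objectives, so the point is not peripheral.

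**Working it through.** **1. Time frame.** Treatment lasts 6 weeks and visit 13 comes 4 weeks after visit 12 (Procedure). 6 + 4 = 10 weeks, which reproduces the stated cycle. The ban covers 6/10 = 60% of it. In the other 40% other care is allowed and can be counted for anyone still under follow-up.

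**2. Overlap of banned and costed care.**

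| Item | Costed? | Named in the ban, weeks 0–6? |
|---|---|---|
| Drugs obtained at clinics or hospitals for CLBP | Yes | Yes, for the listed classes |
| Over-the-counter drugs | Yes | Yes, for the listed classes, e.g. NSAIDs |
| Physical therapy, injections | Yes, where they are clinic or hospital care for CLBP | Yes |
| Supplements, medical and orthotic devices | Yes | Not named |
| Transport, care, time, lost productivity | Yes | No |

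The overlap is real but partial, and it lies in the medical costs. The economic paragraph adopts a healthcare-system perspective, so medical costs are likely to carry much of the weight.

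**3. Planned attrition.** The sample size section inflates 33 per group for 20% dropout: 33/(1 − 0.20) = 41.25, rounded up to 42. The plan thus allows for about 42 × 0.20 = 8.4 dropouts per arm from all causes. It does not say how many would come from use of other care.

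**4. Effect on incremental cost (illustrative).** The documents give neither costs nor usage rates. Assume that a share pC of controls and pT of treated participants are withdrawn for other-care use, that each user's care costs c, that all of it goes unrecorded, and that it is in effect counted as zero.

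- True contribution to incremental cost (treatment minus control): (pT − pC) × c
- Recorded contribution: 0
- Bias = recorded − true = (pC − pT) × c

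| pC | pT | Bias per participant |
|---|---|---|
| 5% | 5% | 0 |
| 20% | 20% | 0 |
| 10% | 5% | +0.05c |
| 20% | 10% | +0.10c |
| 20% | 0% | +0.20c |
| 10% | 20% | −0.10c |
| 0% | 20% | −0.20c |

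The 20% upper end is the planned all-cause dropout rate, so it attributes every planned dropout to this one reason. A positive value makes the combination look more expensive than it is; a negative value makes it look cheaper. With equal use and equal cost per user the lost cost cancels. The table covers cost only. Missing RMDQ and EQ-5D values could also move the denominator of the ICER, and nothing in the documents allows that to be sized.

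**The case against.** The strongest reply is that the documents never say these costs are discarded. The article is silent on whether collection stops at withdrawal and on which population enters the economic analysis. Either may be settled in the full protocol or an analysis plan that is not shown. Changes in medication or treatment are checked at every visit, so the triggering use would probably be noted. The Procedure section has all participants return at visit 13. The full analysis set does not exclude anyone for using other care. Barring co-interventions to protect the pain comparison, with an economic evaluation alongside, is also a recognised trade-off.

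Much of this stands, and it rules out several stronger readings:

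- *Everyone who obtains other care is withdrawn.* The criterion requires both an effect on the results and absence of permission, and the investigator may allow some medications.
- *Other care is what the analysis is meant to cost.* It is only part: intervention-related and non-medical costs count too, as does other care in weeks 6–10.
- *The ICER loses these costs and so understates the value of the herbal medicine.* Loss is an inference, no rates by arm are given, and the sign can go either way.
- *Last observation carried forward will be applied to costs.* That rule is stated for the full analysis set; the economic analysis is described separately.

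What the reply does not remove is the clash between stated rules. Withdrawal for using barred care sits in the same list as loss to follow-up and withdrawn consent, and the text does not say that visit 13 includes withdrawn participants. An analysis plan cannot recover data that were not collected, so what happens after withdrawal has to be fixed in the protocol.

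**Conclusion.** The concern holds in a limited form. Followed as written, the plan can remove a participant because of the event that generates a cost the ICER is meant to include, during 60% of the economic time horizon. This puts later cost, RMDQ and EQ-5D data at risk. Bias in the incremental cost then requires two further conditions: that the data are in fact lost, and that use of other care, or its cost per user, differs between arms. Both are plausible in this design; neither is established by the documents. The direction is open and the size cannot be computed. The −0.20c to +0.20c range rests wholly on assumed usage and complete loss of cost, and it includes zero. The ban itself is a defensible restriction that limits how far the economic result generalises; it is not an error. The point is worth acting on because the remedy is cheap and serves a stated objective.

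**What to change.** Reconcile the Concomitant treatment and Withdrawal criteria sections with the economic outcome and the economic paragraph of the Statistical analysis:

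1. Separate the end of study treatment from the end of data collection.
2. Continue cost, RMDQ and EQ-5D collection to visit 13 for every randomised participant who still consents, whatever other care is used.
3. Count that care as a cost in the assigned arm.
4. Base the ICER on all randomised participants, and let use of barred care affect only membership of the per-protocol set.
5. Report with the economic result that other care was restricted by protocol in weeks 0–6.

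This concerns data collection and analysis only. No change is proposed to the concomitant-treatment rules or to the rules for stopping treatment; reconciling those passages is for the sponsor.

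The cost is protocol wording plus continued follow-up at visits already planned. RMDQ and EQ-5D are already scheduled at visits 4, 8, 12 and 13; the article does not name the visits for cost collection, so these should be stated. Some participants will decline further visits, and cost variance may rise.

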### Safety assessment

Physical examinations will be performed at the screening visit and at visit 1 and 13. Blood chemistry tests including pregnancy tests will be conducted at the screening visit and visit 12. The blood chemistry test will assess the red blood cell (RBC) count, white blood cell (WBC) count, hemoglobin (Hb), hematocrit (Hct), platelet count, erythrocyte sedimentation rate (ESR), aspartate aminotransferase (AST), alanine aminotransferase (ALT), blood urea nitrogen (BUN), creatinine, electrolytes (Na, K, Cl), and C-reactive protein (CRP). Vital signs, adverse events, and change in medication/treatment will be checked at every visit.

### Withdrawal criteria

### The withdrawal criteria are:

Violation of the inclusion criteria or applicable to exclusion criteriaSerious adverse events that make it difficult to maintain the trialRefusal to continue, withdrawal of consent by the participants and/or legal representativeCompliance with Palmijihwang-hwan or acupuncture treatment less than 80% (participants should take more than 23 of the total 28 doses of Palmijihwang-hwan given at the time of the visit and receive more than 10 of the total 12 acupuncture treatments)Violation of the clinical trial protocol by the investigator or the participantsLoss to follow upUse of medications or treatments that affect the results of the trials without the permission from the practitionerInappropriate process as judged by the investigator

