### Interventions

#### Control group intervention

Participants in the control group will receive only the acupuncture treatment. Sterilized stainless steel needles with 0.25 mm width and 40 mm length (DB108C; Dongbang Medical Co., Boryung-si, South Korea) will be inserted at 11 local and 4 distal acupuncture points for 20 min. Acupuncture points are as shown in Table 1. Participants will receive the acupuncture treatment twice a week for 6 weeks, performed by Korean medical doctors who are specialists in acupuncture and moxibustion.

**Table 1 Tab1:** Acupuncture treatment protocol based on the Standards for Reporting Interventions in Clinical Trials of Acupuncture (STRICTA) [29]

1. Acupuncture rationale	1a) Acupuncture technique	Traditional Korean medicine theory
	1b) Reasoning for treatment provided (based on historical context, literature sources, and/or consensus methods), with where appropriate	Textbook of acupuncture and moxibustion and related articles
	1c) Extent of treatment variations	EX-B2 of lesion or upper and lower levels
2. Details of needling	2a) Number of needle insertions per subject per session	Acupuncture points: 15
	2b) Names of points used	Local acupuncture points: GV3, EX-B5/bilateral BL23, BL24, BL25, BL26 (total 11 points) Distal acupuncture points: bilateral BL40, BL60 (total 4 points)
	2c) Depth of insertion based on a specified unit of measurement	20–40 mm
	2d) Response sought	De-qi (penetrating, sharp, aching and painful sensations)
	2e) Needle stimulation	Rotation of the acupuncture needle 3–5 times
	2f) Needle retention time	20 min
	2 g) Needle type	Sterilized stainless steel needle with 0.25 mm width and 40 mm length (DB108C; Dongbang Medical Co., Boryung-si, South Korea)
3. Treatment regimen	3a) Number of treatment sessions	12 sessions
	3b) Frequency and duration of treatment sessions	Twice a week for six weeks (Total 12 times)
4. Other components of treatment	4a) Details of other interventions used for the treatment group	Lifestyle advice about chronic low back pain
	4b) Setting and context of treatment, including instructions to practitioners and information and explanations for patients	Practitioners are instructed to prevent talking with participants
5. Practitioner background	5) Description of participating acupuncturists	Korean medical doctors who are specialist in acupuncture and moxibustion at least three years of experience, or under supervision by a specialist

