#### Treatment group intervention

Participants in the treatment group will receive the same acupuncture treatment as the control group and will also take Palmijihwang-hwan. At visit 1, 4, and 8, they will receive 2-week doses of Palmijihwang-hwan (14 days + an extra 7 days) in an individual package from the practitioners. The Palmijihwang-hwan that will be used in this study is a brown, bitter herbal extract granule produced and packed by Kracie Pharma Korea Co., Ltd. (Seoul, Korea) in accordance with the Korean Good Manufacturing Practice guidelines. Palmijihwang-hwan contains eight herbs (listed in Table 2), is water-extracted with starch and lactose, and is regulated by the Korean Food & Drug Administration. At the production stage, each herb is tested for properties, morphology, and undergoes physicochemical and microorganism examination. Then Palmijihwang-hwan is produced by extraction, separation, concentration, drying, and granulation with compound herbs. Multiple quality tests are performed, including pattern analysis of the ingredients contained to ensure quality and stability, and we will test for residual pesticides to ensure product safety. Palmijihwang-hwan, packed for one dose, will be provided by an independent pharmacist in a separate room and participants will be instructed to take it with water 30 min after breakfast and after dinner, for 6 weeks.

**Table 2 Tab2:** Ingredients of Palmijihwang-hwan

Scientific name	Proportion
*Rehmannia glutinosa (steamed 9 times)*	5.0
*Cornus officinalis*	3.0
*Dioscorea batatas*	3.0
*Alisma orientale*	3.0
*Poria coccos*	3.0
*Paeonia sulffruticosa*	3.0
*Cinnamomum cassia*	1.0
*Aconitum carmichaelii (processed)*	1.0

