### Statistical analysis

Continuous variables at baseline will be expressed as means plus/minus standard deviation and statistically tested using the two-sample *t* test or the Wilcoxon rank sum test. Categorical variables at baseline will be expressed as frequencies and statistically tested using the chi-squared test or Fisher’s exact test. If there is a significant difference between groups, the baseline variable will be considered as a covariate for efficacy analysis.

The full analysis set (FAS) will be analyzed primarily, including participants who take at least one dose of Palmijihwang-hwan and complete at least one pain assessment. Also, the per-protocol set (PPS) will be subordinately analyzed, including participants who take more than 80% of the total Palmijihwang-hwan dose and complete the trial. In the FAS analysis, the missing data will be imputed using the method of last observation carried forward. The primary outcome (change in the VAS score between baseline and endpoint) will be tested by analysis of covariance (ANCOVA) or rank ANCOVA (according to normality or homoscedasticity) with factors of group and study site and covariates of baseline values. Continuous variables for the secondary outcomes will also be tested, respectively, by ANCOVA or rank ANCOVA. Categorical variables for the secondary outcomes will be tested by chi-squared test or Fisher’s exact test according to the number of the cells with a value of 5 or less in the contingency table. Every variable predefined in the outcome sections will be compared at each time point, respectively.

The safety set will include participants who receive at least one dose of Palmijihwang-hwan. In safety analysis, the frequency and ratio of adverse events will be applied and compared between the treatment group and the control group using the chi-squared test or Fisher’s exact test. Any abnormal change in blood chemistry tests from visit 1 to 12 will be expressed as frequency and percentage and compared between the treatment group and the control group using McNemar’s chi-squared test, and any change in vital signs between visit 1 and 12 and between visit 1 and 13 will be expressed as change scores and compared between the treatment group and the control group using the two-sample *t* test or the Wilcoxon rank-sum test. Statistical tests will be carried out at 5% significance level (two-sided), using R software (Version 3.5.0 or later; R Foundation for Statistical Computing, Vienna, Austria).

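### The dose and session counts in the 80% withdrawal rule are, as worded, one unit stricter than 80%

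*Protocol article*

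**What the plan says.** The Withdrawal criteria list, among other reasons, compliance below 80% with either the herbal medicine or the acupuncture. The same item then translates that percentage into counts. For the herb, "participants should take more than 23 of the total 28 doses of Palmijihwang-hwan given at the time of the visit". For acupuncture, participants should "receive more than 10 of the total 12 acupuncture treatments".

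The denominators can be traced elsewhere in the article. Under Treatment group intervention, participants are told to "take it with water 30 min after breakfast and after dinner, for 6 weeks", and supply is handed out by the fortnight at visits 1, 4 and 8. Table 1, under Control group intervention, gives the acupuncture schedule as "Twice a week for six weeks (Total 12 times").

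Statistical analysis sets a related threshold for the per-protocol set, limited to "participants who take more than 80% of the total Palmijihwang-hwan dose and complete the trial". That threshold is a percentage only, with no count attached.

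**The concern.** A withdrawal criterion has to give one answer for each participant. Here the percentage and the counts meant to express it give different answers at one value of each measure: exactly 23 of 28 doses, and exactly 10 of 12 sessions.

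If staff apply the counts as written, the second missed acupuncture session leads to withdrawal, in either arm. If they apply the percentage, only the third does. For the herb, it is the fifth missed dose in a fortnight against the sixth.

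Four hospitals apply the rule, and an independent monitor checks adherence to the protocol at each. Two sites could treat like participants differently, and both could cite the same item. Withdrawal also removes a participant from the per-protocol set, which requires completion of the trial.

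**Working it through.** **Inputs**

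- Compliance limit: withdraw below 80% (Withdrawal criteria).
- Doses per dispensing period: 2 per day × 14 days = 28 (Treatment group intervention). This agrees with the 28 in the withdrawal item.
- Acupuncture sessions: 2 per week × 6 weeks = 12 (Table 1). This agrees with the 12 in the withdrawal item.
- Doses over the whole course: 2 per day × 42 days = 84.

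**Can the stated counts be reproduced from 80%?**

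The lowest compliant count is the smallest whole number not below 0.80 × total.

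- Doses: 0.80 × 28 = 22.4, so 23. Check: 22/28 = 78.6% fails, 23/28 = 82.1% passes.
- Sessions: 0.80 × 12 = 9.6, so 10. Check: 9/12 = 75.0% fails, 10/12 = 83.3% passes.

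Neither 22.4 nor 9.6 is a whole number, so it makes no difference whether the limit is read as at least 80% or as strictly above 80%. Both readings give 23 and 10. The printed numbers are therefore the right cut-offs, but only if each is itself acceptable. *More than* excludes them.

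**The two readings side by side**

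| | 80% rule | Counts read literally | Gap |
|---|---|---|---|
| Lowest acceptable doses of 28 | 23 (82.1%) | 24 (85.7%) | 1 dose, 3.6 points |
| Missed doses allowed | 28 − 23 = 5 | 28 − 24 = 4 | 1 |
| Lowest acceptable sessions of 12 | 10 (83.3%) | 11 (91.7%) | 1 session, 8.3 points |
| Missed sessions allowed | 12 − 10 = 2 | 12 − 11 = 1 | 1 |

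**Against the per-protocol dose threshold**

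Strictly more than 80% of 84 is more than 67.2, so at least 68 doses (81.0%). A participant who takes 23 doses in each of the three fortnights takes 3 × 23 = 69 of 84 (82.1%). That meets the per-protocol dose condition, yet the literal count is failed in every fortnight.

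**Illustration of scale for acupuncture**

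The document gives no attendance rates. The figures below assume independent attendance with the same probability at each of the 12 sessions, and the conclusion does not rest on them.

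| Assumed attendance per session | P(at least 10) | P(at least 11) | Share at exactly 10 |
|---|---|---|---|
| 80% | 0.56 | 0.27 | 0.28 |
| 85% | 0.74 | 0.44 | 0.29 |
| 90% | 0.89 | 0.66 | 0.23 |
| 95% | 0.98 | 0.88 | 0.10 |

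The last column is the difference taken before rounding. Under this simple model the disputed value need not be rare, but no figure for this trial can be inferred.

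**The case against.** The strongest reply is that nothing was miscalculated. The numbers 23 and 10 are the correct whole-number cut-offs for 80%, and only the comparison word is off. The article is loose in the same way under Secondary outcomes: it defines the minimal clinically important difference as a 2 cm fall on the VAS, then restates it as a fall of more than 2 cm. The intended meaning is thus easy to guess. This stands as an account of the cause. It does not remove the conflict, because the text as written still gives two answers.

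Second, the listed criterion can be read as the percentage, with the counts as mere explanation. On that reading nobody at 23 doses or 10 sessions is withdrawn. This is fair, and it is why the consequences above are stated as conditional on the counts being applied. The article does not say which half governs, however, and a count is the easier half for a site to apply.

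Third, the 69-of-84 example is not a separate contradiction with the per-protocol definition. That definition also requires completion, so a withdrawn participant fails it whatever the dose. This stands: the example shows a consequence of the ambiguity and is not a second error.

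Fourth, the effect on the analysis is limited. The full analysis set is primary and is defined by one dose and one pain assessment, so withdrawal for compliance does not by itself remove anyone from it. The per-protocol analysis is subordinate. This also stands.

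Lastly, the full protocol used at the sites is not shown and may be worded precisely. That is possible, but the published sentence needs correcting either way.

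**Conclusion.** The concern holds, as a minor point. Read literally, the counts ask for 85.7% of doses and 91.7% of sessions, where the lowest counts that satisfy the stated 80% are 82.1% and 83.3%. The discrepancy is one dose in 28 and one session in 12, and it affects only participants at exactly those values. How many that would be cannot be stated from the document.

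The conclusion rests on the ordinary meaning of *more than* and on denominators that the article confirms. Sample size, power and alpha are unaffected. Any effect on the primary analysis would depend on outcome assessment stopping at withdrawal, which the withdrawal item does not say.

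**What to change.** In the compliance item of the Withdrawal criteria, replace *more than* by *at least* twice, so that it requires at least 23 of the 28 doses and at least 10 of the 12 acupuncture sessions. Both counts then match the stated 80%.

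The cost is one phrase changed in two places. No new data are needed, and visits, sample size and analysis stay as they are. If the full protocol has the same wording, the correction belongs there too and should go to all four sites, so that the rule is applied in the same way.
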